## Abstract

**Background:**

Total knee replacement (TKR) surgeries have increased in recent years. Exercise programs and other interventions following surgery can facilitate the recovery process. With limited clinician contact time, patients with TKR have a substantial burden of self-management and limited communication with their care team, thus often fail to implement an effective rehabilitation plan.

**Objective:**

We have developed a digital orthopedic rehabilitation platform that comprises a mobile phone app, wearable activity tracker, and clinical Web portal in order to engage patients with self-management tasks for surgical preparation and recovery, thus addressing the challenges of adherence to and completion of TKR rehabilitation. The study will determine the efficacy of the TKR platform in delivering information and assistance to patients in their preparation and recovery from TKR surgery and a Web portal for clinician care teams (ie, surgeons and physiotherapists) to remotely support and monitor patient progress.

**Methods:**

The study will evaluate the TKR platform through a randomized controlled trial conducted at multiple sites (N=5) in a number of states in Australia with 320 patients undergoing TKR surgery; the trial will run for 13 months for each patient. Participants will be randomized to either a control group or an intervention group, both receiving usual care as provided by their hospital. The intervention group will receive the app and wearable activity tracker. Participants will be assessed at 4 different time points: 4 weeks before surgery, immediately before surgery, 12 weeks after surgery, and 52 weeks after surgery. The primary outcome measure is the Oxford Knee Score. Secondary outcome measures include quality of life (Short-Form Health Survey); depression, anxiety, and stress (Depression, Anxiety, and Stress Scales); self-motivation; self-determination; self-efficacy; and the level of satisfaction with the knee surgery and care delivery. The study will also collect quantitative usage data related to all components (app, activity tracker, and Web portal) of the TKR platform and qualitative data on the perceptions of the platform as a tool for patients, carers, and clinicians. Finally, an economic evaluation of the impact of the platform will be conducted.

**Results:**

Development of the TKR platform has been completed and deployed for trial. The research protocol is approved by 2 human research ethics committees in Australia. A total of 5 hospitals in Australia (2 in New South Wales, 2 in Queensland, and 1 in South Australia) are expected to participate in the trial.

**Conclusions:**

The TKR platform is designed to provide flexibility in care delivery and increased engagement with rehabilitation services. This trial will investigate the clinical and behavioral efficacy of the app and impact of the TKR platform in terms of service satisfaction, acceptance, and economic benefits of the provision of digital services.

**Trial Registration:**

Australian New Zealand Clinical Trials Registry (ANZCTR) ACTRN12616000504415; https://www.anzctr.org.au/Trial/Registration/TrialReview.aspx?id=370536 (Archived by WebCite at http://www.webcitation.org/6oKES0Gp1)

## Introduction

### Overview

Rates of total knee replacement (TKR) procedures have been rising steadily worldwide in recent years [1]. There has been an 80% increase in TKR procedures in Australia since 2003 [1-3], with increasing incidence and prevalence likely to continue due to factors such as the aging population, an increase in obesity and joint injury, and expectations of a continued physically active lifestyle, as well as higher demand for surgery at a younger age [1,4,5]. The mean age of TKR patients in Australia is 69 years; however, the demand for the surgery in the younger population (less than 65 years) has been increasing and is expected to double in the next decade [3,6-8].

Research has shown that a number of interventions prior to TKR surgery can improve outcomes or patient’s satisfaction [9,10]. Physiotherapy undertaken before TKR is effective in improving postoperative outcomes [10]. Quadriceps muscle stretching and upper body exercises before the procedure allow patients to be prepared for the postoperative condition and rehabilitation physiotherapy program [10]. Managing patient expectation prior to surgery has been shown to benefit the rehabilitation process and is an important predictor of postoperative outcomes [11,12]. To prepare patients for their TKR surgery and hospital stay, preoperative education may offer advantages for some patients when stratified according to their physical, psychological, and social conditions [13]. Moreover, interventions that help reduce comorbidities and obesity prior to surgery can have postoperative impact, such as improved recovery and reduced chances of adverse events [2].

Most TKR patients experience pain, joint stiffness, insufficient muscle strength, and limited physical activity after surgery [14]. Early mobility following surgery has been shown to improve functional mobility and prevent deep vein thrombosis [2,15]. Studies have shown that postoperative rehabilitation can improve short-term outcomes (3-4 months) with no significant difference between different types of treatment, however the benefits of longer term rehabilitation (4-12 months) are limited [16,17]. Postoperative physiotherapy (6-8 weeks) is common practice in Australia [1], but adherence to physiotherapy programs can be low. Adherence can be low because of pain during exercise and low levels of activity prior to surgery but also because of social and psychological issues such as low self-efficacy, depression, anxiety, and poor social support [18].

Clinicians require information from their patients for diagnosis and monitoring recovery. Many of these indicators are self-reported by the patients, such as completion of physiotherapy, functionality, pain, and sleep quality. Another key measure of progress used by physiotherapists and surgeons is range of motion (ROM), a measure of the flexibility of the knee joint [16].

We are looking at ways to motivate and assist patients to complete rehabilitation programs to realize proven benefits and improve TKR surgery outcomes. We propose a solution in the form of a digital orthopedic rehabilitation platform aimed at supporting patients and their clinicians across phases of TKR, from expectation management when considering TKR surgery right through to patient recovery and rehabilitation.

Our TKR platform comprises a mobile phone app used daily in conjunction with a wrist-worn activity tracker and a clinical Web portal. The aim is to address the challenges of engaging patients with information and physical exercise through self-managed tasks delivered via the app in surgical preparation and recovery and to bridge the communication gap between clinicians and patients via the clinical Web portal. The app is designed to assist patients in achieving meaningful behavior change around uptake, adherence, and completion of rehabilitation programs, along with meaningful education, self-monitoring, and behavior coaching through rich media content.

This paper introduces the TKR platform and details the research protocol of a study to determine the efficacy and associated impact of the platform in assisting patients in their preparation for and recovery from the TKR surgery. An Australian multisite (N=5) randomized controlled trial (RCT) will be conducted for this purpose. The duration of the study is expected to be 24 months, which includes in-hospital setup and staff training, participant recruitment, intervention delivery, and data analysis. The trial will run for 13 months for each patient.

### Total Knee Replacement Platform Technology

The design and functionality of the TKR platform have been informed through a user needs analysis. The user needs analysis (paper forthcoming) included interviews and focus groups with patients (n=11), general practitioners (n=8), orthopedic surgeons (n=12), and physiotherapists (n=3). The results of the analysis from the qualitative data clearly identified different stages of the TKR journey, each with different needs and priorities, which has informed the design of our platform technology for TKR. The qualitative data was used to refine features and functionalities of the platform, which comprises a patient facing app and activity tracker and a clinical Web portal for use by clinical care teams.

The information delivered via the app been scientifically validated and all exercise videos were created in conjunction with expert physiotherapists working with TKR patients.

In order to foster motivation, the purpose-built app for iOS and Android devices includes weekly psychoeducation sessions and tasks that are delivered by a program guide via text and voice recordings. This content is also reinforced through tasks (eg, goal-setting) that the user can complete outside of the app (eg, on paper). This motivational content was developed using self-determination theory [19] and included techniques designed to foster positive emotions [20]. Tools to assist in behavior change in the app use commonly identified behavior change techniques, such as self-monitoring, goal setting and reviewing, and rewarding/recognizing achievements that appear in various behavioral models which can be broadly encompassed by social cognitive theory [21,22].

The clinical Web portal is designed for clinicians to monitor patient progress and configure physiotherapy programs. Patient data, gathered by the app, is transmitted to the portal for review by members of a patient care team. Physiotherapy programs for each patient are configured from a library of videos typically used for TKR rehabilitation. Once set, programs are available to patients in their app. Figure 1 provides sample screenshots of the TKR platform.

**Figure 1 figure1:**
[figure not shown]
Total knee replacement platform. Left: app used daily in conjunction with a wrist-worn activity tracker. Right: clinical Web portal.

## Methods

### Overview and Aims

Data will be collected as part of a 13-month (for each participant), multisite unblinded RCT where participants are assigned to 1 of 2 study groups (1:1 allocation ratio). Both groups will undergo TKR surgery and be offered usual care and guidance from their surgeon and nominated health care team. In addition, the intervention group will receive the TKR app and a Garmin Vivosmart HR activity tracker. Patient participants will be scheduled for TKR surgery and managed through a project officer (PO), typically a member of the clinical team. Participants in the intervention group will be provided with instruction from the site PO in regard to using the technology. The aims of the study are as follows:

To determine the efficacy of the TKR platform in delivering clinical and behavioral outcomes by specifically evaluating group differencesTo understand the impact of the TKR platform components and level of satisfaction with surgery and the care deliveryTo evaluate economic benefits

The study includes an active intervention period commencing when the patient is scheduled for surgery (approximately 4 weeks before surgery) and ending when the patient is 12 weeks postoperative. This is followed by a 40-week free-living period, finishing 1 year after surgery. Paper-based questionnaires will be completed by participants and the PO will be responsible for collecting responses from participants at 4 time points as illustrated in Figure 2.

All access to data will be controlled by authentication and authorization protocols designed to ensure the data is protected and only accessible by authorized persons. All information identifying the participants will be de-identified by a member of research team.

**Figure 2 figure2:**
[figure not shown]
Study design: outcome measures, procedure, and timeline.

### Participants

#### Recruitment

Patients scheduled for TKR surgery at trial sites will be screened by surgeons for clinical eligibility. Those who meet eligibility requirements will be informed of the study by the site PO and screened for technical eligibility (eg, access to iPhone/iPad, smartphone/tablet, Internet access). Recruitment will be conducted by the PO and coordinated by the Clinical Trial Coordinator (CTC). Figure 3 summarizes the processes involved in the recruitment and enrollment of patients, trial data collection, and data administration.

**Figure 3 figure3:**
[figure not shown]
Process and workflow: patient recruitment, enrollment, trial data collection, and data administration.

#### Selection Criteria

Patients meeting the criteria as evaluated by the operating surgeon will be approached for recruitment by the PO. Inclusion criteria include:

patients aged between 50 and 80 yearssuffering osteoarthritis as the principle diagnosis and reason for TKRscheduled to undergoing unilateral knee replacement (using commercial partner prosthesis) for the first time on one of the kneessufficiently healthy to not be adversely affected by participation in the trialdeemed suitable candidates for physiotherapy both pre- and postsurgeryhave access to a smartphone/tablet (iOS or a leading Android-based device) with Internet connection via mobile Internet data or Wi-Fi connectionwilling to participate in the study and to have assessments on 4 occasions in line with scheduled appointments with their cliniciansbe sufficiently proficient in the English language to not be affected by participation in the trial

Exclusion criteria include:

bilateral knee replacementprevious unicompartmental replacement or tibial osteotomy on the same knee or previous lower extremity joint replacement surgery within the last 6 monthsmajor neurologic conditions or cognitive impairment that may result in inability to interact with the smartphone appuncontrolled diabetes, heart disease, or other medical conditions indicating participation in TKR is nonstandard

Based on the age criteria, surgeons will determine health-related eligibility of patients as well as assessing patient’s neurological condition using standard clinical practice.

### Randomization

#### Procedure

Eligible participants at each site will be randomized to 1 of the 2 treatment groups by a member of the research team. A simple randomization allocation technique in blocks of 10 using a randomization table generated by computer software will be used. Each site will have an intervention (ie, TKR platform) and a control group.

Participants will be randomized according to individual trial sites because usual care at each hospital (ie, trial site) will differ. Some hospitals offer presurgery education, others use online resources, and some offer daily outpatient rehabilitation classes or facilities such as hydrotherapy pools and gymnasiums. Other hospitals discharge patients to the community where they can privately engage services.

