### Outcome Measures

#### Overview

Basic demographic data and a brief history of medical/health conditions will be taken at baseline. PO will be responsible for collecting responses from participants, either face-to-face at the clinic or received by post. OpenClinica (www.openclinica.com) will be used to store digital copies of responses from self-reported questionnaires, which include validated and trial specific questionnaires. The patient diaries and audit questions for health care providers will inform the economic outcomes for this study. Patient diaries will be documented online using SurveyGizmo (www.surveygizmo.com).

Interviews will be conducted with a selected number of patients, their carers, and clinicians in order to capture outcomes related to the TKR platform technology with regard to service delivery satisfaction and usability. Table 1 summarizes the outcome measures, the data collection tools and procedures, and the time points. The remainder of this section details the various outcome measures.

**Table 1 table1:** Outcome measures, data collection tools and procedures, and timeline.

Outcome		Measurement tool/procedure/ data collection	Time points (weeks)			
			*Baseline*	*0*	*12*	*52*

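### A single fixed block size of 10 within each site lets a project officer who keeps a tally know about one allocation in six in advance: a modest, avoidable risk of selection bias

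*Protocol article*

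**What the plan says.** All references are to the protocol article.

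- **Method** (Randomization, Procedure): "A simple randomization allocation technique in blocks of 10 using a randomization table generated by computer software will be used". No other block size and no variation in size is mentioned.
- **Stratification** (same section): "Participants will be randomized according to individual trial sites because usual care at each hospital (ie, trial site) will differ".
- **Who assigns** (same section): "Eligible participants at each site will be randomized to 1 of the 2 treatment groups by a member of the research team".
- **Blinding and ratio** (Overview and Aims): the trial is a "multisite unblinded RCT where participants are assigned to 1 of 2 study groups (1:1 allocation ratio").
- **Project officer (PO), position** (Overview and Aims): patients are "managed through a project officer (PO), typically a member of the clinical team".
- **PO, recruitment** (Recruitment): "Recruitment will be conducted by the PO and coordinated by the Clinical Trial Coordinator (CTC"). The PO also screens for technical eligibility. Surgeons screen for clinical eligibility.
- **PO, intervention** (Overview and Aims): "Participants in the intervention group will be provided with instruction from the site PO in regard to using the technology".
- **PO, data** (Outcome Measures, Overview): "PO will be responsible for collecting responses from participants, either face-to-face at the clinic or received by post".

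**The concern.** There are two separate faults.

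The first is the label. Simple randomization means independent allocations with no restriction, whereas blocks of 10 are a restriction. The two terms in the sentence name different methods, and only the second fits the rest of the section.

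The second is predictability. With one known block size, the end of each block follows from its beginning. Nobody is blinded, and the PO who teaches the app to one arm at a site can tell who was allocated to which arm there. The same PO approaches and screens the next patient. If the PO can foresee that patient's arm, the decision to approach, how hard to encourage, or the timing may come to depend on it, even unintentionally. The primary outcome, the Oxford Knee Score (OKS), is self-reported in an unblinded trial. A difference between arms in the kind of patient enrolled could therefore be mistaken for an effect of the platform.

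**Working it through.** **Inputs.** Block size 10, 1:1, so b = 5 places per arm (Procedure; Overview and Aims). Five sites, 262 patients stated as sufficient, 320 expected at most (Sample Size). Equal site sizes are my assumption.

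**The plan's own figure.** The article gives no figure for predictability. The 262 used as a denominator can be reproduced: per arm, 2 × (0.5 × (1.960 + 0.842)/0.15)² × (1 + 3 × 0.5)/4 = 109.0. Two arms × 1.2 for loss gives 261.6, or 262. The planned effect in that scenario is 0.15/0.5 = 0.30 SD.

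**Step 1: allocations known with certainty in a completed block.** Once one arm's five places are used, all remaining places are determined. The expected number is 2b/(b + 1) = 10/6 = 1.67 of 10, or 16.7%. Enumerating all C(10,5) = 252 sequences gives the same value. The last place is always determined. The last two or more are determined in 2 × C(8,3)/252 = 112/252 = 44% of blocks.

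**Step 2: over the trial.** A last block with fewer than five patients contributes nothing, because neither arm can yet be exhausted.

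| Total | Per site | Completed blocks per site | Known with certainty |
|---|---|---|---|
| 262 | 52.4 | 5 | 5 × 5 × 1.67 = 41.7, about 42 |
| 320 | 64 | 6 | 5 × 6 × 1.67 = 50 |

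If every block were completed, the counts would be 262/6 = 44 and 320/6 = 53.

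**Step 3: best guess.** Always guessing the arm with more places left is right b + (2^(2b)/C(2b,b) − 1)/2 = 5 + (1024/252 − 1)/2 = 6.53 times in 10 (65.3%).

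**Step 4: what steering could do.** Suppose the PO's choice shifts a patient's expected score by ±g SD, in the direction of the foreseen arm. Acting only on certain allocations biases the arm difference by 1.67g/5 = 0.33g. Acting on every guess biases it by (2 × 6.53 − 10)g/5 = 0.61g. The documents give no g. For an assumed range of 0.05 to 0.30 SD, the bias before covariate adjustment is 0.02 to 0.10 SD in the first case and 0.03 to 0.18 SD in the second, against the planned 0.30 SD. These are upper-end values, since they suppose steering at every opportunity.

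**Step 5: effect of varying the block size.** I simulated sites of 64 patients.

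- *Certainty.* For an observer who knows the sizes in use and has the full allocation history, fixed blocks of 10 make 15.5% of allocations certain (the 50/320 of Step 2, within simulation error). Random sizes 8/10/12 make 1.4% certain, about 4 of 320. That is the figure if the set of sizes leaks; an observer ignorant of the set has still less to go on.
- *Best guess.* It is 64.7% for fixed 10 and 64.8% for 8/10/12. It is 66.1% for 6/8/10, 67.8% for 4/6/8 and 63.2% for 10/12/14/16. Varying the size removes certainty but not the drift back to balance, and small mixed blocks make guessing easier.

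**The case against.** The strongest defence is the separation of roles. A research team member, not the PO, assigns the arm, and only eligible patients are randomized. Surgeons decide clinical eligibility, entry is tied to the surgery date, and device and Internet access is required of both arms. Ten is also a fairly large block: fixed blocks of four would make 33% of allocations certain. No passage says sites are told the block size. Details of concealment may properly sit in the full protocol, and the figure showing the enrolment workflow is not available here.

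Much of this stands. A reader might infer that the PO makes or hands out the allocation, or that allocation is unconcealed. The documents support neither: they give the PO technology instruction only, and their silence on concealment is not a fault in an article. PO discretion over whom to approach and when is a reasonable inference from the recruiting role, not a stated fact.

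What does not stand is that separate assignment closes the route. Someone who knows past allocations and the block size can count without seeing the list, and the article prints the block size.

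A reader might also infer that any imbalance would pass straight into the OKS difference. It would not. The Statistical Analysis section adjusts for the baseline measure, sex and motivation, with hospital as a random effect. The protection is partial, because adjustment removes only what measured covariates carry. Table 1 lists the Self-Motivation Inventory at week 0 only, about four weeks after the intervention starts, and lists no measure of the technology literacy that the Discussion names as a barrier.

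**Conclusion.** The point holds as a modest, avoidable risk of selection bias arising from what the article states: one block size, blocking by site, no blinding, and one person who both recruits and learns earlier allocations. It is not evidence that selection bias occurred.

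The size is 16.7% of allocations known with certainty in a completed block, or about 42 of 262 or 50 of 320. This assumes a PO who knows the block size, keeps an accurate tally and works at one of five equal sites.

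It is tempting to set the 65% best-guess rate against 50% and present the difference as what better blocking would recover. That is not supported: 50% belongs to unrestricted randomization, and varying blocks leave the rate at roughly 63% to 68%.

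The use of *simple* for a blocked scheme is a plain error of description and holds without any of these assumptions.

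**What to change.** For all remaining enrolment:

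1. Replace the fixed blocks with site-stratified permuted blocks of randomly varying size, not smaller on average than now (for example 8, 10 and 12), and keep the sizes undisclosed to sites.
2. Assign the arm only after consent and baseline measures are recorded. If the full protocol already requires this, a sentence confirming it is enough. This step matters in its own right, because varying the sizes does not lower the best-guess rate.
3. Describe the method as stratified permuted-block randomization and delete *simple*.
4. Record the date on which each open site changes lists.

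The cost is a new computer-generated list and a short amendment. The Results section says one site began in October 2016 and the others were expected in early 2017, so an early change would cover most patients. The downside is a slightly larger possible imbalance at a site that stops mid-block: at most 12/2 = 6 patients instead of 10/2 = 5.
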